## Abstract

**Introduction:**

Glioblastoma is an aggressive primary brain tumor with poor survival. Depressive and anxiety symptoms and suicidality are common and impair quality of life and care. Prospective multicenter data using validated measures of suicidal ideation and behavior in German glioblastoma cohorts are scarce. We aim to quantify psychiatric symptom burden and suicidality and examine associations with demographic, clinical, and tumor-related characteristics.

**Methods:**

SHINE-GLIO is a multicenter, cross-sectional observational study at German neuro-oncology centers. Adults with newly diagnosed isocitrate dehydrogenase wild-type glioblastoma after primary radiotherapy and before first recurrence are eligible. Exclusion criteria include clinically significant aphasia, other malignancies, and known tumor predisposition syndromes. At one outpatient visit, participants undergo physical examination and complete validated self-report questionnaires assessing suicidality (SSEV), depressive symptoms (PHQ-8), anxiety (GAD-7), social support (SUCE−4), and quality of life (EORTC QLQ-C30 and QLQ-BN20). Tumor characteristics, clinical history, and concomitant medications are extracted from medical records. Prespecified regression models will examine associations with suicidality while accounting for demographic, clinical, and tumor-related factors.

**Perspective:**

This study will provide a standardized multicenter assessment of suicidality and related psychiatric symptoms in German patients with glioblastoma. The findings may inform screening and referral pathways for mental health care.

**Trial registration:**

ClinicalTrials.gov identifier: NCT07409584. First posted prospectively on February 12, 2026.

## Introduction

Glioblastoma is an aggressive primary brain tumor with an unfavorable prognosis. In unselected contemporary cohorts, median overall survival is generally between 12 and 18 months, whereas selected molecular subgroups may experience substantially longer survival [1–3]. It remains among the solid tumors with the shortest survival despite multimodal therapy. Management of newly diagnosed glioblastoma typically includes maximal safe tumor resection, followed by combined radiotherapy and temozolomide chemotherapy. In selected patients, treatment may be supplemented with tumor-treating fields. Since the introduction of radiotherapy plus temozolomide in 2005, only a small number of randomized phase III trials have demonstrated an overall survival benefit in newly diagnosed glioblastoma, largely driven by alkylating regimens rather than targeted or immune therapies [1]. Nearly all patients ultimately develop disease progression despite initial therapy.

At recurrence, management is individualized and may include repeat surgery, reirradiation, and systemic agents, but evidence is heterogeneous and no universally accepted overall-survival–prolonging standard exists [4]. Given the poor prognosis and high neurological morbidity, a glioblastoma diagnosis can profoundly disrupt emotional well-being, physical function, and social roles [5, 6]. Compared with many other cancers, brain tumors uniquely threaten cognition, communication, behavior, and autonomy, complicating decision-making and social participation [7, 8]. Psycho-oncological consultations frequently reveal high psychological burden, with many patients expressing concerns about death and a strong need for medical information [9]. Hence, patients with glioma frequently experience psychiatric comorbidities such as depression and anxiety, which are associated with diminished quality of life and may negatively affect treatment adherence and survival. By comparison, suicidality remains understudied and is rarely assessed in a standardized manner [10–13]. Depressive symptoms may reflect direct neurobiological and treatment-related effects (e.g., lesion location, inflammation, corticosteroid exposure) and/or a psychological response to diagnosis and functional loss [11]. Longitudinal trajectories of depression and anxiety after surgery are heterogeneous, with some patients improving transiently and others worsening as treatment burden and neurological disability accumulate [14, 15].

Suicide mortality is elevated in cancer patients compared with the general population, with the magnitude of risk varying by cancer type and being particularly high in poor-prognosis tumors [16]. Data on suicidality in glioblastoma specifically are limited. Large population-based analyses indicate higher suicide mortality after cancer diagnosis, with risk varying by tumor type and time since diagnosis; poor-prognosis central nervous system (CNS) malignancies consistently rank among higher-risk groups [17]. Existing literature suggests that suicidality in brain tumor populations likely reflects interacting neuroanatomical, treatment-related, inflammatory, and psychosocial factors, although evidence is heterogeneous and often observational. While inflammatory biomarkers such as tumor necrosis factor alpha (TNF-α) and interleukin-6 (IL-6) have shown associations with suicidal ideation in psychiatric samples, evidence regarding their significance in glioblastoma is limited, and tumor-specific studies are needed to clarify their role [18–21].

Registry-based analyses report low absolute numbers of death by suicide in malignant brain tumor patients, but interpretation is limited by ascertainment, follow-up time, and the fact that suicidal ideation is rarely captured in such datasets. In registry studies, higher suicide mortality has been associated with demographic factors (e.g., male sex and older age) and tumor-related characteristics (e.g., supratentorial location), although findings may reflect confounding and may not generalize across healthcare systems and populations. Adjusted registry models suggest that suicide mortality may be highest within the first year after diagnosis and is associated with age, sex, and tumor location, although causality cannot be inferred [22]. Another U.S. population-based analysis likewise reported that suicide deaths are rare events in brain tumor registries and appear more frequent in older male patients and in glioblastoma, underscoring the need for studies that directly measure suicidal ideation and behavior [23]. A systematic review reported that suicidal ideation is substantially more common than suicide attempts in brain tumor populations [24], but estimates vary widely across studies due to heterogeneous measurement tools, timepoints, and tumor subtypes. Across heterogeneous studies, suicidal ideation and behavior have been associated with depressive and anxiety symptoms, functional impairment, and selected demographic and tumor-related characteristics, although endpoint definitions differ substantially.

However, suicide mortality estimates from administrative registries are vulnerable to misclassification and under-ascertainment, and their generalizability to contemporary Central European healthcare settings remains uncertain. Most datasets also do not assess how many individuals experienced significant suicidal ideation without progressing to recognized suicide.

Diagnosis of high-grade glioma often causes significant psychosocial stress in affected patients. Even structured distress screening strategies have shown limited impact on downstream psychosocial care uptake, highlighting implementation gaps relevant to mental health risk detection. The GLIOPT study investigated whether screening for distress based on physician–patient conversations was improved in the intervention group compared with the control group, which completed only the Distress Thermometer. In that trial, the endpoint focused on the number of patients with impaired emotional functioning who received specialized psychosocial care, rather than on suicidality-specific outcomes [25]. This underscores that generic distress screening alone may be insufficient to trigger appropriate psychosocial interventions, supporting the need for suicidality-specific assessment in glioblastoma.

Functional impairment in intracranial tumor patients may coincide with greater psychological burden, supporting the inclusion of performance status as a potential correlate of suicidality. In a German longitudinal cohort, 21.5% of participants reported suicidal thoughts at least once during follow-up, although estimates are limited by tumor heterogeneity and measurement approach. Reported suicidal ideation fluctuated over follow-up timepoints, with peaks in some subgroups, but subgroup-specific estimates are difficult to generalize to glioblastoma. That study suggested that suicidal thoughts can occur across different intracranial tumor histologies, alongside reduced health-related quality of life, although generalizability is limited [26]. Against the backdrop of these findings, our planned study will examine suicidality in a multicenter design, focusing on glioblastoma patients, with slightly modified endpoints in light of the current WHO CNS classification.

In summary, depression, anxiety, and suicidality constitute clinically relevant and potentially under-recognized comorbidities in glioblastoma care. Population-based studies suggest increased suicide mortality in malignant brain tumor populations, while suicidal ideation is likely far more prevalent yet less systematically measured. Nevertheless, available data remain limited, and prospective studies are scarce.

## Methods

### Aim of the study

This multicenter, cross-sectional observational study aims to assess associations between suicidality and clinical and psychological variables in patients with glioblastoma. Validated questionnaires will assess anxiety, depression, disease-specific health-related quality of life, and social support. The primary endpoint is suicidality during the past four weeks, measured at the single study visit using the SSEV score. Secondary endpoints include anxiety symptoms (GAD-7), depressive symptoms (PHQ-8), health-related quality of life (EORTC QLQ-C30 and EORTC QLQ-BN20), and social support (SUCE−4). The findings are intended to inform the design of future supportive-care interventions for depression, anxiety, and suicidality in glioblastoma.

### Study design

Approval for this prospective, multicenter observational study was granted by the Ethics Committee in Essen, Germany (approval no. 25—12,746-BO), and all participating sites obtained local ethical approval before enrolling participants. The study will recruit 180 patients diagnosed with glioblastoma. Manuscript preparation followed the STROBE (Strengthening the Reporting of Observational Studies in Epidemiology) reporting guidelines. To ensure feasibility and reduce burden on participants, all assessments are scheduled within one outpatient visit. The study is conducted in accordance with the Declaration of Helsinki and applicable national legislation.

### Study procedures

Patients can be included in the study after completion of primary radiotherapy and before the first recurrence (local MRI assessment according to RANO 2.0 [27]). After being informed about the study objectives during a physician consultation, patients provide written informed consent prior to enrolment. Questionnaires are completed independently by participants without the presence of relatives. During a single outpatient visit, trained staff perform a standardized clinical and neurological assessment, including Karnofsky Performance Status. Participants also complete the predefined self-report instruments listed in Table 1, which are administered under strictly standardized self-completion conditions. If, when completing the SSEV questionnaire, at least one question is answered with “less than once a week” or more often, further evaluation will be conducted during a medical consultation on the same day, and based on its results the patient will be referred to psycho-oncological care. Patient data are obtained from medical records by a clinical investigator based on a standardized case report form (demographics, diagnosis/tumor data, previous cancer treatment, MRI findings, medical history, medication, vegetative symptoms, substance use, family history of cancer) and the study visit. The recruitment period runs from March 18, 2026, through March 17, 2028. As the primary study center, Essen is expected to recruit approximately 60 participants, or 30 per year. The remaining approximately 120 participants in the planned total sample of approximately 180 participants, including anticipated dropouts, will be recruited across the other participating centers. Each center is expected to recruit approximately 10–20 participants over the two-year recruitment period. The regular follow-up of patients with glioblastoma at these specialized centers provides an established population from which potentially eligible participants can be screened. Based on these ongoing clinical follow-up structures and the multicenter design, recruitment of the planned study population by March 17, 2028, is considered feasible.

**Table 1 Tab1:** Overview of study endpoints

Endpoints	Measure	Brief description
*Primary*		
Suicidality	Scale for Suicidal Experience and Behavior (SSEV) [28]	The SSEV is a 9-item self-report questionnaire assessing suicidal thoughts, impulses, intentions, plans, and attempts within the past four weeks. The primary outcome will be a continuous composite score based on the first six items (range 0–18), with higher scores reflecting greater suicidal ideation severity. The 6-item score was selected to ensure a standardized and sensitive measure across participants Secondary and sensitivity analyses will include a dichotomized version of suicidal ideation (score ≥1 on the 6-item scale, indicating presence vs. absence). Lifetime suicide attempts will be assessed separately using a single yes/no item and treated as a secondary outcome
*Secondary*		
Depressive symptoms	Patient Health Questionnaire−8 (PHQ-8) [30]	Depressive symptoms are measured by the validated German PHQ-8, with responses on a 0–3 Likert scale (“0-not at all” to “3-nearly every day”). Scores will be analyzed continuously and categorized into standard severity levels (minimal to severe). The PHQ-8 was preferred over the PHQ-9 to avoid inclusion of a suicidality item and thus prevent overlap with outcome measures in suicidality analyses
Anxiety symptoms	Generalized Anxiety Disorder-7 (GAD-7) [31]	Anxiety is assessed using the GAD-7, with standard response options from 0 (“not at all”) to 3 (“nearly every day”) and established cutoffs for mild (≥ 5), moderate (≥ 10), and severe (≥ 15) anxiety
Health-related quality of life (disease-specific)	EORTC QLQ-C30 [32] and EORTC QLQ-BN20 [33]	Quality of life is assessed using the EORTC QLQ-C30, a 30-item instrument evaluating general cancer-related quality of life. In addition, the EORTC QLQ-BN20 is used to capture brain tumor–specific symptoms and functional impairments, including visual problems, communication difficulties, future uncertainty and motor dysfunction
Social support	Short Questionnaire on Social Support in Chronic Illness (SUCE−4) [29]	The SUCE−4 is a brief instrument assessing perceived social support in individuals with chronic illness. All four items are assessed on a 5-point Likert scale and coded numerically (0 to 4 from ‘no’ to ‘yes’), with any assistance during completion and any missing items documented according to prespecified rules. The “social support” score ranges from 0 to 16 and is the sum of all four items
Physical impairments/disabilities	Physical Examination / Medical Records	Physical impairments and disabilities are assessed through a standardized clinical and neurological examination and review of the medical records. Relevant impairments, including motor, sensory, visual, language, and other neurological deficits, as well as their impact on functional status, will be documented
Tumor location	Medical records/MRI	The MRI closest to the study visit (within a prespecified time window) will be used to code tumor location using predefined anatomical categories (cerebellum, brainstem, temporal, frontal, parietal, occipital, basal ganglia, or spinal)
Marital status	Social History	Marital status is recorded during the medical interview as part of the social history. The interview follows standard demographic conventions [34]

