### Outcome measures

#### Medical history/assessment of concomitant medication and comorbidities

A medical history covering recorded previous illnesses (both psychiatric and somatic), past surgeries, allergies, intolerances, current and past medications, use of stimulants or addictive substances based on the participant’s statement, family and social history, as well as subjective side effects of previous tumor-specific treatments based on the participant’s statement and medical records will be obtained during the study visit.

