#### Statistical analyses

Associations between suicidality and candidate predictors will be examined using regression models appropriate to the distribution of the SSEV outcome, defined as the continuous 6-item SSEV composite score assessing suicidal ideation during the past four weeks. Depending on distributional properties, linear regression models will be used for approximately continuous and symmetric outcomes, while generalized models will be considered in case of marked skewness or zero inflation. All assumptions (including linearity, homoscedasticity, and distribution of residuals) will be assessed and reported where applicable. Prior to multivariable modeling, descriptive statistics and bivariate correlations (Pearson or Spearman, depending on scale properties and distribution) will be computed to describe the data structure. These analyses are purely exploratory and will not be used for variable selection. Multicollinearity will be assessed using variance inflation factors (VIF).

As secondary and sensitivity analyses, additional models will be fitted using (a) a dichotomized suicidal ideation outcome (presence vs. absence of suicidal ideation, defined as a 6-item SSEV score ≥ 1) and (b) lifetime suicide attempts assessed by the dedicated dichotomous SSEV item. These analyses will include the same set of predictors and are intended to assess the robustness of findings across alternative operationalizations of suicidality. All analyses are considered exploratory and hypothesis-generating and are not intended to establish causal relationships.

Given the exploratory nature of the study, all prespecified candidate predictors will be entered simultaneously into a multivariable model without prior univariable screening. To reduce overfitting and improve the stability of estimates in the presence of a relatively high number of predictors, penalized regression (ridge regression with tuning via cross-validation) will be applied. Model performance will be internally validated using bootstrap resampling (e.g., 5,000 resamples) to estimate and correct for optimism in performance metrics. Regression coefficients with 95% confidence intervals will be reported, along with model performance measures such as R^2^ and root mean squared error (RMSE) for the continuous outcome.

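### The same-day evaluation trigger is defined only by frequency answers, so a 'yes' on the lifetime suicide-attempt item does not by itself lead to an evaluation

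*Protocol article*

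**What the plan says.** Under Study procedures, the protocol article makes same-day evaluation depend on the SSEV answers. The condition opens "If, when completing the SSEV questionnaire, at least one question is answered with", and the answer it then names is a frequency category: less than weekly, or anything more frequent. When it is met, "further evaluation will be conducted during a medical consultation on the same day, and based on its results the patient will be referred", the destination being psycho-oncological care.

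Table 1 describes the SSEV as a nine-item self-report of suicidal experience and behaviour over the past four weeks, with a primary score built from the first six items (range 0–18). The same row adds: "Lifetime suicide attempts will be assessed separately using a single yes/no item". It is a secondary outcome.

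The Statistical analyses section lists two further outcomes: (a) a six-item score of at least 1, and (b) "lifetime suicide attempts assessed by the dedicated dichotomous SSEV item". The models for both are "intended to assess the robustness of findings across alternative operationalizations of suicidality".

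The section on medical history provides for "A medical history covering recorded previous illnesses (both psychiatric and somatic"), to be taken at the study visit. It states no action that follows from what is found.

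**The concern.** The study asks every participant whether they have ever attempted suicide and analyses the answer as a form of suicidality. The safety rule, as printed, does not respond to that answer. Whether a disclosed attempt is followed up on the day then depends on how the history is taken at each site, not on a rule.

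This is not confined to attempts from decades ago. Patients enter after completing primary radiotherapy, and the SSEV is described as covering the past four weeks. An attempt made after the glioblastoma diagnosis but more than four weeks before the visit lies outside that window. On the article's description, the lifetime item is the only question certain to capture it. The Introduction itself notes that suicide mortality may be highest in the first year after diagnosis and that reported ideation fluctuates over follow-up. Quiet answers for one four-week period therefore do not settle the matter for someone who discloses an attempt.

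A private self-report may also be where an attempt is first mentioned, since the questionnaires are completed without relatives present.

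**Working it through.** The article gives no figure to reproduce. The check compares the trigger with the answer format of the item.

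1. **Trigger (Study procedures).** It is met when at least one SSEV question receives an answer at or above a stated frequency category.
2. **Item format (Table 1; Statistical analyses).** The lifetime-attempt item has 2 possible answers, yes and no. Answers that are a frequency at or above the threshold: 0 of 2.
3. **Is the item inside the rule's scope?** The Statistical analyses section calls it an SSEV item. Table 1 says it is assessed separately and does not say whether it is one of the nine.
   - If it is one of the nine, the rule covers the questionnaire it belongs to, but its answer format cannot satisfy the condition.
   - If it is not one of the nine, a rule confined to the SSEV questionnaire does not reach it.
   - The result is the same in both cases.
4. **Test case.** Every frequency item is below the threshold and the lifetime item is 'yes'. No answer is at or above the threshold frequency, so the trigger is not met.
5. **Other routes.** The medical history may bring an attempt to light, but no evaluation or referral step is tied to it. No other section attaches an action to a 'yes'.
6. **Comparison of the two alternative outcomes.**
   - Outcome (a): six items with a range of 0–18 give 18 / 6 = 3 points per item if all are scored equally. The threshold category is then plausibly the lowest non-zero answer, so a score of at least 1 would also meet the trigger. This is an inference, because the form is not shown.
   - Outcome (b): a positive answer cannot meet the trigger.
   - So 1 of the 2 alternative outcomes has no evaluation step attached.
7. **Number of sites applying the rule.** About 120 participants are expected from centres other than Essen, at 10–20 each: 120 / 20 = 6 to 120 / 10 = 12 further centres. Each would handle a 'yes' at its own discretion.

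The article gives no frequency of lifetime attempts, so no share of the 180 participants is computed.

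**The case against.** The strongest reply has four parts.

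- **This is a condensed article.** The full protocol, site instructions and SSEV form are not shown and may contain a wider procedure. That is true and limits confidence. But the article does not leave the trigger to another document. It prints one, and the point concerns the reach of that printed rule.
- **The rule is a sufficient condition, not an exclusive one.** It does not tell sites to ignore a 'yes', and clinicians remain free to act. This stands: the gap is that no evaluation is required, not that one is forbidden.
- **A same-day consultation is meant for current risk.** The threshold is low, and a past attempt with no current ideation need not call for urgent action. Much of this stands. A lifetime attempt does not prove current suicidality, and using it as a regression outcome does not make it an acute warning sign. It does not cover the attempt made after diagnosis but before the four-week window, which most clinicians would want to ask about.
- **A clinical contact already exists at the visit.** A history is taken and an examination performed, so the opportunity to evaluate is there. This stands too, and it is why the remedy is cheap. An opportunity is not the same as an instruction.

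None of these makes the printed trigger reach a 'yes'.

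**Conclusion.** The concern holds as a gap in the wording of a stated safety rule. A 'yes' on the lifetime-attempt item, with all frequency items below the threshold, requires no evaluation under the article as printed. Its extent is 0 of 2 answer options able to meet the trigger; the number of participants affected is unknown.

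The conclusion rests on the article alone, and confidence is moderate because site documents may already cover the case. The formats of the SSEV items outside the six-item score, apart from the yes/no item, are also unknown, and a recent attempt may well be caught by one of them. The point is an improvement worth making rather than a flaw that threatens the study.

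**What to change.** Extend the trigger in Study procedures and in the site instructions, for example: 'A medical consultation takes place on the same day if any SSEV frequency item reaches the stated threshold, or if the lifetime suicide-attempt item is answered yes.' Keep referral dependent on the result of that consultation, as the article already does, so that a remote attempt leads only to a short clinical check. If the full protocol or site instructions already contain this, it is enough to confirm it.

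The cost is one clause, plus a brief same-day conversation with some participants whose attempt was long ago. No additional visit is needed, because a medical history is already taken at the study visit.
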